**Exclusion criteria**
Walked an average of ≥10,000 steps a day in the 4 weeks before V0 (must be verifiable by pedometer, etc)Wearing a pacemakerUsing continuous glucose monitoring (but do not exclude if self-monitoring of blood glucose level or intermittently scanned continuous glucose monitoring was conducted ≥8 weeks before V0)Diagnosed with hyperthyroidism and have received treatment other than thyroid hormone replacement in the year before V0Diagnosed with a moderate to severe heart condition that requires exercise restriction as assessed by a physicianRequire exercise treatment restrictions as assessed by a physician at V0—decision made with reference to “Cases in which exercise therapy should be prohibited or restricted” in the Guidelines for Diabetes Treatment (Japan Diabetes Society; 2022-2023)Hemoglobin <10 g/dL in the 12 weeks before V0Serum albumin ≤3 g/dL in the 12 weeks before V0Diagnosed with preproliferative retinopathy or retinopathy of a later stage within the year before V0Cannot undergo exercise treatmentPregnancy, including any possibility or intention of pregnancyParticipation in other trials at the time of initial registration (V0)Impaired cognitive function, as determined by the investigator or subinvestigatorAny other reason that the patient is classified as unfit for participation by the investigator or subinvestigator (a record must be maintained about the reason the patient was determined to be ineligible)

### Intervention Process

The study (Table 2) includes 10 events (V0-V9), a 24-week continuous measurement phase (M), and a 12-week follow-up observation phase. Initial measurements will be made at event V0. At V0, we will provide each participant with a near field communication–enabled pedometer (A&D; UW-204NFC) and an iPhone (iPhone 8 with iOS 16) prepared with the placebo app configured for step count only. We will direct the participants to wear the pedometer throughout the day except during sleep. We will use the step count gathered during V1 to confirm eligibility and to set a step count baseline.

The surveys that will be used in this study are listed in Textbox 4.

**Table 2 table2:** Study events—1 measurement period and 10 visits spanning approximately 37 weeks.

Event	Focus	Time	Key activities
V0	Physical baseline assessments and initial registration	Enrollment—≥7 days before the beginning of the intervention	Collect consent Collect demographic information: date of birth, sex, smoking and drinking status, medical history, diet and exercise habit, household living condition, employment, use of smartphones, habit of step count measurement, and stage of behavior change according to the transtheoretical model of change regarding walking 10,000 steps a day Collect physical data: blood tests to measure HbA_1c_^a^, FBG^b^, LDL^c^ cholesterol, HDL^d^ cholesterol, TG^e^, and eGFR^f^; urinalysis; and height, body weight, and BP^g^ measurements Collect medication and combination therapy status Assess health literacy Conduct surveys (Textbox 4) Distribute pedometer and placebo-equipped phone
V1	Step count baseline	From V0 to the day before V2 (at least 7 days)	Patients record daily steps and determine step count baseline
V2	Registration, allocation, and beginning of the intervention	Beginning of the intervention (end of week 0)	Measure HbA_1c_ level Finalize registration and allocation Distribute BP monitor and scale Activate all placebo and StepAdd features Collect medication and combination therapy status Check for adverse events
M	Ongoing measurement	From V2 to V8	Daily measurements via app Intervention only: daily feedback, weekly feedback, and weekly personalized goal setting via app Check for defects
V3	Hospital visit 1	End of week 4	Check app use and equipment Check for adverse events Intervention: coach goals and coping strategies Collect medication and combination therapy status
V4	Hospital visit 2	End of week 8	Check app use and equipment Check for adverse events Intervention: coach goals and coping strategies Collect medication and combination therapy status
V5	Interim hospital visit	End of week 12	Collect physical data: blood tests to measure HbA_1c_, FBG, LDL cholesterol, HDL cholesterol, TG, and eGFR; urinalysis; and body weight and BP measurements Check app use and equipment Check for adverse events Intervention: coach goals and coping strategies Collect medication and combination therapy status Conduct surveys (Textbox 4)
V6	Hospital visit 4	End of week 16	Check app use and equipment Check for adverse events Intervention: coach goals and coping strategies Collect medication and combination therapy status
V7	Hospital visit 5	End of week 20	Check app use and equipment Check for adverse events Intervention: coach goals and coping strategies Collect medication and combination therapy status
V8	End of the intervention	End of week 24	Collect physical data: blood tests to measure HbA_1c_, FBG, LDL cholesterol, HDL cholesterol, TG, and eGFR; urinalysis; and body weight and BP measurements Collect medication and combination therapy status Check for adverse events Conduct surveys (Textbox 4) Assess usefulness and usability
V9	End of follow-up	End of week 36	Collect physical data: blood tests to measure HbA_1c_, FBG, LDL cholesterol, HDL cholesterol, TG, and eGFR; urinalysis; and body weight and BP measurements Collect medication and combination therapy status Check for adverse events Conduct surveys (Textbox 4)

^a^HbA_1c_: hemoglobin A_1c_.

^b^FBG: fasting blood glucose.

^c^LDL: low-density lipoprotein.

^d^HDL: high-density lipoprotein.

^e^TG: triglyceride.

^f^eGFR: estimated glomerular filtration rate.

^g^BP: blood pressure.

Surveys—9 surveys assessing type 2 diabetes–related behaviors and outcomes.
**Problem Areas in Diabetes**
20 items to assess type 2 diabetes–related emotional distress [45]
**Locomo 25**
25-question risk assessment to evaluate musculoskeletal disorders such as walking disability, difficulty in daily living, or pain in the body [46]
**Evaluation Scale for Self-Management Behavior Related to Physical Activity of Type 2 Diabetic Patients**
Assessments of the following:Self-management behavior to enhance daily physical activitySelf-management behavior to maintain the level of physical activity [47]
**Steps achieved**
Self-Efficacy Scale relative to achieving the targeted daily steps [48]
**Dealing with barriers to achieving the targeted daily steps**
Self-Efficacy Scale relative to dealing with barriers to achieving the targeted daily steps [49]
**Physical Activity Self-Regulation Scale–12; Japanese version**
Addresses self-monitoring, goal setting, eliciting social support, reinforcement, time management, and relapse preventionRated from 1 (never use strategy) to 5 (use strategy very often)Scores are the sum of the 2 individual item scores and summed self-regulation subscale scores for a measure of overall self-regulation [50]
**The Summary of Diabetes Self-Care Activities Measure; Japanese version**
Assesses type 2 diabetes self-care activities [51]
**Health behavior “active coping behavior with disease”**
Self-Efficacy Scale for health behavior “active coping behavior with disease” subscale [52]
**Audit of Diabetes-Dependent Quality of Life; Japanese version**
Assesses type 2 diabetes–dependent quality of life [53]

Following randomization, we will begin the intervention. We will provide participants a Bluetooth-enabled sphygmomanometer (A&D; UA-651BLE Plus) and a Bluetooth-enabled weighing scale (A&D; UC-352BLE; in addition to the already provided pedometer and phone). For the control group, we will enable BP and BW measurement functions in the placebo app. For the intervention group, we will replace the placebo app with StepAdd and define the initial goals and barriers. Both the intervention and control groups will watch a video regarding lifestyle modification, self-management of T2D, and effect of exercise on glycemic control.

The main part of the intervention is the daily measurement by all patients throughout phase M. We will direct participants to measure their BW and BP daily upon awakening and wear the pedometer throughout the day except during sleep. All the participants will log the measurement data by syncing the recording devices (weighing scale, sphygmomanometer, and pedometer) to the app, rather than by manually inputting the data. These data are then uploaded to the server and made visible to health care professionals via the administrative screen. Intervention group participants receive personalized feedback about their step count performance 4 times a day. At the end of each week, intervention group participants review their weekly step count performance on the app, determine their personal barriers to achieving the step goals, and identify the possible coping strategies. StepAdd then provides a personalized step goal recommendation for the following week.

Every 4 weeks (events V3-V7), both groups will meet with a physician who will advise patients regarding lifestyle modifications and use of the app and, for the intervention group only, help with goals and coping strategies. Baseline measurements (other than collection of some background information) are repeated at the interim (V5), at the end of the intervention (V8), and at the end of the follow-up observation period (V9). We will collect the equipment at V8, before the follow-up observation period. The purpose of the observational period is to assess whether the intervention-induced effects are maintained after the end of the intervention.

During the study, we will not restrict the use of supplements and drinks that can affect blood glucose level and BP. In both the intervention and control groups, T2D treatment details, such as changes or additions of oral T2D medications, insulin, and glucagon-like peptide–1 receptor agonists and changes in medication dosage, can be changed at the discretion of the attending physician.

If patients discontinue the trial or stop using the app, we will define this as discontinuation, and we will collect the measurements within 7 days of this discontinuation. If participation in the study is discontinued during the intervention period, we will collect the V8 measurement items. If participation in the study is discontinued during the observation period, we will collect the V9 measurements items, except for urinalysis.

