### Outcome Measures

#### Primary Outcome

The primary outcome of this study is the between-group differences in the change of HbA_1c_ value between baseline (V2) and either the end of the intervention period (week 24 [V8]) or, for patients who discontinue before V8, the point of discontinuation. Reduction of HbA_1c_ level by 0.35 percentage points is considered to be clinically significant [54,55].

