**App assessments**		
	20^n^	App use is assessed through the following: Recording rate of body weight, step count, and BP and its change^o^ Goal achievement rate^p^ Goal increment rate^q^ Goal reduction rate^r^ Average number of coping planning strategies implemented per day^s^ Number of barrier identifications^t^
	21^u^	System feasibility and usability (only for the intervention group)
	22^v^	Number of emails, SMSs, and calls to encourage registration

^a^HbA_1c_: hemoglobin A_1c_.

^b^Includes both differences between week 0 (registration at V2) and week 12 (V5; or point of discontinuation, if earlier) and between week 0 (registration at V2) and week 36 (V9; or point of discontinuation, if earlier), which are compared within group and between groups, and includes the difference between week 0 (registration at V2) and week 24 (V8; or point of discontinuation, if earlier), which are compared within group.

^c^Includes all 3 proportions that are compared between groups: latest HbA_1c_ level up to week 12 (V5; or point of discontinuation, if earlier) <7%, latest HbA_1c_ level up to week 24 (V8; or point of discontinuation, if earlier) <7%, and latest HbA_1c_ level up to week 36 (V9; or point of discontinuation, if earlier) <7%.

^d^Includes all 3 differences: between provisional registration (V0) and week 24 (V8; or point of discontinuation, if earlier), between provisional registration (V0) and week 12 (V5; or point of discontinuation, if earlier), and between provisional registration (V0) and week 36 (V9; or point of discontinuation, if earlier), which are compared between groups.

^e^FBG: fasting blood glucose.

^f^eGFR: estimated glomerular filtration rate.

^g^Includes differences between the beginning of the intervention (V2; or from baseline period [V1] for steps) and week 4 (V3) and differences between each visit and each subsequent visit, which are compared between groups. In addition, they include measurements at each period (between visits), which are to be compared between groups. Item 11 also includes difference between baseline (V1) and 2 weeks before week 12 (V5; or point of discontinuation, if earlier) and week 24 (V8; or point of discontinuation, if earlier), which are compared within group and between groups.

^h^BP: blood pressure.

^i^HDL: high-density lipoprotein.

^j^LDL: low-density lipoprotein.

^k^TG: triglyceride.

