### Statistical Analysis

In this study, we define 3 analysis populations: full analysis set (FAS), per protocol set (PPS), and safety analysis set (SAS). FAS is the set of all patients whose data were obtained at least once after randomization. We will follow the intention-to-treat principle and analyze data based on the assigned group in the FAS analysis. PPS is the FAS population with the exclusion of patients who were found to have violated the eligibility criteria after randomization or who did not use the app over a 3-week period. SAS is the set of all patients who used the StepAdd app or the placebo app at least once after randomization. In the safety analysis using SAS, we will analyze data based on the apps actually used by the patients, regardless of allocation. AS will be the primary analysis population, and PPS will provide supportive results. All safety analyses will be conducted in SAS.

Data about patients’ characteristics will be presented as mean, SD, minimum, 25th percentile, median, 75th percentile, and maximum for continuous variables and as frequency and proportion for categorical variables.

In the primary analysis, we will perform between-group comparison of the change in HbA_1c_ level from week 0 (V2) to week 24 (V8; or point of discontinuation, if earlier) using analysis of covariance, including baseline HbA_1c_ level (ie, HbA_1c_ level at week 0 [V2]) as a covariate in FAS. If participants discontinue the study, the latest measurement of HbA_1c_ level before V8 will be used.

We will also conduct 2 subgroup analyses with one classification by HbA_1c_ level at week 0 (V2; either <8.5% or ≥8.5%) and the other classification by BMI at the time of initial registration (V0; either <25 kg/m^2^ or ≥25 kg/m^2^). We will conduct subgroup analysis on the primary outcome in each analysis set to investigate whether the efficacy of StepAdd is consistent between these subgroups.

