In this study, we have elected to use a “formidable” control [60] using a fairly high-functioning placebo app. We have initial confirmation of proof of concept from the pilot, and now, we want to show whether our specific behavior change intervention methods are superior to simply giving patients access to their step count, BW, and BP. There is evidence suggesting that simply giving patients a pedometer increases their activity level [61]; thus, there is some risk that the study will induce a response in the control group, which may prevent statistical proof of any superiority of the StepAdd intervention. Most people who want a pedometer already have access to one in their smartphone, and we think this risk is modest. By giving the placebo group a functional app, albeit one lacking StepAdd’s functionality, we have designed the study to give strong proof of the success of StepAdd, if in truth, it is effective.

Many behavior interventions show solid, short-term gains that fade later [62]. Our StepAdd pilot [29] showed results that continued to improve throughout the study, with no sign of fading. This study expands the trial time to 24 weeks with a 12-week observation period to examine whether the pilot results hold true over a long period. Behavior change maintenance is theorized as an outcome of active and ongoing self-regulation, and habit development follows a period of successful self-regulation of a new behavior [63]. Our objective is to change behavior in a sustainable way, such that the new pattern of behavior becomes a habit that can be sustained over the long haul.

A key to our approach is ensuring that the patients receive a strong introduction to the mechanics of the intervention and the StepAdd app. Patients have busy lives, and we work to make it clear and easy for them to meet the demands of the intervention. By providing training regarding the intervention and the app and by ensuring that all messaging in the intervention is simple and focused, we maximize the likelihood that the patients will use the tools of the intervention just as we intend them to.

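### Stopping the app is classed as discontinuation, so app adherence decides when the primary HbA1c is read, and an early value can stand for week 24 and week 36

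*Protocol article*

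**What the plan says.** All references are to the protocol article.

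- **Intervention Process, discontinuation paragraph.** Two different events share one label: "If patients discontinue the trial or stop using the app, we will define this as discontinuation". For both, "we will collect the measurements within 7 days of this discontinuation", and "If participation in the study is discontinued during the intervention period, we will collect the V8 measurement items". No later measurement is described for these patients.
- **Primary Outcome.** The change runs from V2 to V8 or, "for patients who discontinue before V8, the point of discontinuation".
- **Statistical Analysis, primary analysis.** The ANCOVA takes the change to V8 or to discontinuation if that comes first, and adds: "If participants discontinue the study, the latest measurement of HbA_1c_ level before V8 will be used".
- **Statistical Analysis, populations.** "We will follow the intention-to-treat principle and analyze data based on the assigned group in the FAS analysis".
- **Table 3, footnotes b to d, and the secondary analyses.** The same substitution applies to HbA1c change, laboratory values and questionnaires at weeks 12, 24 and 36. For the responder outcome the wording is "latest HbA_1c_ level up to week 36 (V9; or point of discontinuation, if earlier) <7"%.
- **Abstract, Methods.** The primary outcome is described as the HbA1c change at 24 weeks, with no alternative time point.

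**The concern.** Read together, these rules make the time of the primary measurement depend on whether the patient keeps using the assigned app. One patient's value may come from week 5 and another's from week 24, and the ANCOVA treats both as the same quantity.

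Stopping the app is a response to the treatment. StepAdd asks for weekly goals, barriers and coping reports, while the placebo app mainly records, and the trial is open-label. Stopping could therefore differ between arms in rate or timing, although the article gives no figures. The Introduction itself says that engagement with mHealth tends to fall over time.

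The consequence is plainest at week 36. The observation period exists to see whether effects last after the intervention ends. Under the footnotes to Table 3, a value taken within days of stopping the app, before V8, can be counted as the week-36 result. For that patient, maintenance is assumed and not observed.

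**Working it through.** **1. The plan's own figure.** Inputs from Patient Recruitment: difference 0.35, SD 0.74, two-sided 0.05, power 80%, dropout 10%.
- Normal formula: n = 2 × (0.74 × (1.960 + 0.842) / 0.35)² = 70.2, so 71 per arm.
- Two-sample t-test: 71.1, so 72 per arm, as stated.
- 72 / 0.90 = 80 per arm, 160 in total, as stated.

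The sample size is not in dispute.

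**2. Which value is used.** Table 2 schedules HbA1c at V0, V2, V5, V8 and V9 only. For a patient who stops the app before V8:
- if the 7-day sample is obtained, that fresh early value is analysed;
- if it is missed, the latest earlier value is week 12 (V5) or, for a stop before week 12, baseline, which gives a change of zero.

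The article does not say how long a gap in use counts as stopping. The per-protocol set uses a 3-week gap. If stopping were recognised only after such a gap, the 7-day window, counted from last use, would already have passed.

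**3. Bias against a week-24 value in everyone.** Let d be the share of StepAdd patients who stop, f the fraction of the effect they hold when they stop, and g the fraction they hold at week 24. Then

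bias = 0.35 × d × (f − g).

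The effect is overstated if gains fade after stopping (f > g) and understated if f < g. The standard error with 80 per arm is 0.74 × √(2/80) = 0.117. Rejection when the true week-24 difference is zero is P(|Z + bias/0.117| > 1.96).

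| Assumption | Bias (points) | Two-sided rejection |
|---|---|---|
| 10% stop, 0.35 held then lost | 0.10 × 0.35 = 0.035 | 6.0% |
| 10% stop, 0.3 held then lost | 0.10 × 0.3 = 0.03 | 5.8% |
| 20% stop, 0.35 held then lost | 0.20 × 0.35 = 0.070 | 9.2% |
| 20% stop in StepAdd only, 0.5 held then lost | 0.20 × 0.5 = 0.10 | 13.7% |

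The last row is 0.10/0.35 = 29% of the target difference.

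**4. Bias with no treatment effect at any time.** Suppose both arms fall by 0.5 over 24 weeks and stoppers' values are taken before any change. The spurious difference is (difference in stopping rates) × 0.5.
- 15% vs 5% stopping: 0.10 × 0.5 = 0.05, rejection 7.1%.
- 30% vs 10% stopping: 0.20 × 0.5 = 0.10, rejection 13.7%.
- Equal rates and timing: no bias, rejection 5%.

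Here the error counts against whichever arm stops more. None of the stopping rates, the 0.5-point benefit or the common 0.5-point fall comes from the article.

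**The case against.** The case for leaving the rule alone has real strengths.

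- **Follow-up is not stated to end.** A reader might infer that stopping the app ends outcome follow-up. The text requires a measurement within 7 days and does not cancel V5, V8 or V9. What it fixes is which value is analysed.
- **Allocation is respected.** A reader might infer that the analysis is not by intention to treat at all. The plan says patients are analysed by assigned group, and nothing contradicts that. The departure is in the timing of the outcome.
- **It is not simply last observation carried forward.** The value is normally a fresh sample at a declared time. An old value is carried only when that sample is missed, so the complaint that imputed data are treated as real applies mainly there.
- **The large figures need strong assumptions.** The 13.7% in the one-sided case needs stopping at twice the planned 10% dropout, a gain above the target among those who disengage, full reversal, and no week-24 difference overall. The 12-week pilot retained 97%, although retention is not the same as app use.
- **A power argument does not isolate the rule.** If 10% of patients stop before gaining any effect, 0.35 becomes 0.315 and power with 80 per arm is about 77%. Those patients would probably show little effect at week 24 too, so an as-randomised week-24 analysis would largely share that loss.
- **The remark on fading is general.** "Many behavior interventions show solid, short-term gains that fade later" describes other interventions, and sustainability is a secondary question here.
- **Detail may sit in an analysis plan not shown.** That holds for imputation methods. It does not cover the definition of discontinuation or the endpoint rule, which the article states outright.

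These points narrow the concern. They do not remove the dependence of outcome timing on adherence, or the use of pre-V8 values at week 36.

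**Conclusion.** The concern holds in this limited form. As written, app adherence decides when the primary HbA1c is read, and an early value is analysed as week 24 and may stand for week 36. This conflicts with the 24-week outcome in the abstract and falls short of intention-to-treat follow-up, though not of analysis by allocation.

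Neither size nor direction can be found from the article, because stopping rates by arm are not given. At 10% stopping with the full 0.35 effect lost afterwards, the bias is about 0.035 points, a tenth of the target, with rejection about 6%. It grows with higher or unequal stopping; 0.10 points and 13.7% is an extreme case and not an expectation. With no treatment effect and equal stopping in both arms there is no bias, but nothing in the design secures equal stopping.

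This should be fixed. The trial is described as confirmatory, and a V8 sample that was never drawn cannot be recovered at analysis.

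**What to change.** 1. Define stopping the app and withdrawing from the study as separate events. Reconcile the point at which non-use counts as stopping with the 3-week gap in the per-protocol definition.
2. Seek the scheduled V5, V8 and V9 HbA1c from every randomised patient who still consents, whether or not the app is in use, and analyse those values as randomised.
3. For values that are truly missing, use a baseline-adjusted MMRM on V5 and V8, or multiple imputation followed by the planned ANCOVA.
4. Keep the point-of-discontinuation rule as a sensitivity analysis only.
5. Do not use pre-V8 values for week 36.
6. Bring the Abstract, the discontinuation paragraph, Primary Outcome, the Table 3 footnotes and Statistical Analysis into line.

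**Cost.** The visits are already scheduled, so the added burden is the effort to bring back patients who stopped the app. But this amends the primary endpoint definition while recruitment is under way (44 patients by September 5, 2023). Patients already discontinued may lack V8 values, and the estimate may be less favourable to StepAdd.
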